
##### Incremental cost-effectiveness ratio at 6 months

The incremental cost-effectiveness ratio at 6 months will be calculated from the cost differential of the strategies and the efficiency differential defined by the rate of good responder patients in each group. The ICER and the 6 months will be subjected to a deterministic and probabilistic sensitivity analysis.

##### *Protomic secondary outcome measures*

Description of the variation of the proteomic profile

The biomarkers of the proteomic profile will be compared between the inclusion visit (M0) and the 6-month visit, as well as the differences in both the M0 and M6 visits between the two treatment arms.

The comparison will be done by biomarker. The biomarkers will be described at each time (indicators and boxplot) globally, as well as by the observed response group. The risk of the first species *α* is fixed, by convention, at 5% for the different comparative analyses.

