### Objectives {7}

The primary objectives of this clinical trial is to study the clinical and pharmacoeconomic impact after 6 months of the use of the SinnoTest® predictive tool in patients with rheumatoid arthritis who have failed to a first anti-TNF biologic agent compared to usual care. The secondary objectives will be:
Pharmacoeconomic: to carry out a budget impact analysis (BIA) at 6 and 12 months;Clinical: to describe the performance of the software’s predictive model on new clinical data from the 6-month trial.

We will also carry out a proteomics substudy with the objectives of comparing the variation of the proteomic profile between the M0 (date of inclusion) and the M6 (end of study date). The achievement of this objective will be based on the constitution of a biobank, which will serve as a basis for future studies focused on the therapeutic management of these patients.

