### Interventions

#### Explanation for the choice of comparators {6b}

##### Intervention description {11a}

The patients will be randomized to an intervention group (SinnoTest®) or an active-control group (usual care). Patients allocated to the intervention arm will receive the prescription of bDMARD (rituximab, adalimumab, abatacept) using SinnoTest® software, while those allocated to the control arm will receive the prescription of bDMARD without the SinnoTest® software which corresponds to current practice (all bDMARDs).

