##### Innovative procedure

*Innovative Medical Device (IMD): SinnoTest® Software version 2.0*

SinnoTest® is a therapeutic guidance device for patients suffering from chronic inflammatory rheumatism, in particular RA. SinnoTest® consists of the following three elements: “routine” biological assay of biomarkers from a blood sample, calculation algorithm, and graphical user interface (software and online application). This device was designed by the company Sinnovial. The assessment of its conformity was carried out by SurgiQual Institute.

Biomarkers are detected and quantified in blood samples of patients, using commercial tests aimed at determining the levels of these molecules. These results are sent to the SinnoTest® secure server. These data are processed by algorithms to determine the probability of response to the treatments available in the therapeutic arsenal (biological therapies). These algorithms were developed in a population of patients with a previous failure to iTNFs receiving the specific medication the algorithm was designed for. This data is sent to a secure server. The graphical user interface is an independent software, accessible through a web platform, which allows authorized health professionals to access the results of the analysis of individual patients. SinnoTest® is a stand-alone IMD-MD software, accessible via a web platform. Rheumatologists from the different centers will be contacted by email to register for the SinnoTest® online platform. A link in this email will provide access to the registration part of the application. The rheumatologists will then be able to connect to the SinnoTest® platform thanks to their personal identifiers.

*Process of the innovative procedure*

The selection of the bio-drug is carried out based on the recommendations of SinnoTest®. This test categorizes bDMARD based on the probability of response. It will allow to prescribe both original molecules and biosimilars in an equivalent way. In the SinnoTest® arm, the investigator prescribes the treatment defined as the most effective by SinnoTest®, except in case of contraindication. If contraindicated, the investigator prescribes the second-choice treatment (if any) of SinnoTest® in terms of efficacy.

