##### *Proteomic secondary outcome measures*

Description of the variation of the proteomic profile between M0 (biotherapy start date) and M6 (6 months visit) (time frame: inclusion and 6 months)

Based on shotgun and semi-quantitative proteomics, the differences between the proteomic profile at baseline and at M6 will be analyzed.

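### The proteomic arm comparison at M6 is stated without the patient's own M0 level; adjusting for it would gain precision at no cost

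*Protocol article*

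**What the plan says.** All references are to the Protocol article.

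- **Aim.** Objectives {7} gives the substudy's purpose as "comparing the variation of the proteomic profile between the M0 (date of inclusion) and the M6 (end of study date". Outcomes {12}, under the proteomic secondary measures, says that "the differences between the proteomic profile at baseline and at M6 will be analyzed".
- **Analysis.** The proteomic part of Statistical methods (headed Protomic secondary outcome measures) names two comparisons in one sentence. The first is over time: "The biomarkers of the proteomic profile will be compared between the inclusion visit (M0) and the 6-month visit". The second is between arms: "as well as the differences in both the M0 and M6 visits between the two treatment arms". Biomarkers are described at each time "globally, as well as by the observed response group". The type I error "is fixed, by convention, at 5% for the different comparative analyses".
- **Contrast within the article.** For disease activity, quality of life and disability, the statistical section states that all models are adjusted for baseline variables and that a time-by-arm interaction is examined. For software performance it plans results overall and for each biotherapy. The proteomic paragraph states neither.
- **Drugs.** Intervention description {11a} gives the intervention arm "prescription of bDMARD (rituximab, adalimumab, abatacept) using SinnoTest® software" and the control arm any bDMARD. The section on the innovative procedure adds a wider fallback for intervention patients in whom the software recommends nothing.

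**The concern.** The substudy asks how the profile changes from M0 to M6, but the stated arm contrast does not address change. It sets the arms side by side at M0 and again at M6.

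In a randomised trial the M0 comparison can show only chance imbalance. The M6 comparison is where the M0 sample would help, because a patient's earlier level usually explains part of the later one, and there its use is not stated. The result is a wider confidence interval than the collected data allow, for every biomarker tested.

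There is also a point of interpretation. The arms choose from different sets of drugs, so the drugs actually given may differ between arms. A biomarker that moves with a particular drug could then differ between arms without any difference in response.

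**Working it through.** **1. The plan's own figure.** The substudy states no sample size, SD, M0–M6 correlation or power. The only sample size is that of the main trial (Sample size {14}): 65% against 65 + 18.2 = 83.2%, two-sided 5%, 80% power. With the pooled-variance formula and no continuity correction,

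n = [1.960·√(2·0.741·0.259) + 0.842·√(0.65·0.35 + 0.832·0.168)]² / 0.182² ≈ 90 per group.

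It reproduces. It matters here only as an upper bound: at most 90 per arm can enter the substudy, because participation is optional.

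**2. Precision of the M6 arm contrast.** Take SD = 1, n = 90 per arm and correlation ρ between M0 and M6 (assumed).

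- M6 only: variance factor 1.
- M6 adjusted for M0 (ANCOVA): factor 1 − ρ².
- Change from M0: factor 2(1 − ρ).

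The detectable difference at 80% power is (1.960 + 0.842)·√(2/90) = 0.418 SD for M6 only. For the other two methods it is multiplied by the square root of the factor.

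| ρ (assumed) | ANCOVA factor | Unadjusted ÷ adjusted variance | Detectable, M6 only | Detectable, ANCOVA | Detectable, change | ANCOVA power at 0.418 SD |
|---|---|---|---|---|---|---|
| 0.3 | 0.91 | 1.10 | 0.418 | 0.398 | 0.494 | 83.6% |
| 0.5 | 0.75 | 1.33 | 0.418 | 0.362 | 0.418 | 89.9% |
| 0.7 | 0.51 | 1.96 | 0.418 | 0.298 | 0.323 | 97.5% |

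At each of these values ANCOVA is the most precise of the three. Raw change is worse than M6 alone below ρ = 0.5, equal at 0.5 and better above it. The ratio of variances does not depend on n, so it holds for a smaller substudy too.

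**3. Can drug mix alone move the arm contrast?** Suppose a biomarker differs by D SD between the three software drugs and all others, whatever the response. The arm difference is then D × (intervention share − control share). The Discussion puts use of the three drugs in practice at up to 49%; take that as the control share. D and the intervention share are assumptions. SD is held at 1, with 90 per arm and two-sided 5%.

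| Intervention share | D = 0.5: difference, power | D = 1: difference, power |
|---|---|---|
| 60% | 0.055 SD, 6% | 0.11 SD, 11% |
| 80% | 0.155 SD, 18% | 0.31 SD, 55% |
| 100% | 0.255 SD, 40% | 0.51 SD, 93% |

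The range runs from practically the nominal 5% to near certainty. Drug mix can produce an arm difference with no response difference behind it, but it may equally be negligible. The article does not let one say which.

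**The case against.** The strongest defence is that this is a descriptive outcome of an optional substudy, reported in a condensed article, and that covariates and strata for such an analysis are commonly left to a fuller document. For the drug breakdown that defence stands. For the arm contrast it stands only in part, because the article does state the comparison to be made, and does state baseline adjustment for the clinical outcomes in the same section. The wording is loose enough that an arm comparison of changes could be meant. That would be a reason to clarify it, and step 2 shows that raw change is still less precise than ANCOVA at the correlations considered.

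Three stronger readings are tempting, and the article does not support them.

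- **That M0 is ignored altogether.** A reader might infer this from the arm comparison alone, but the same sentence compares M0 with M6. Only the arm contrast lacks M0.
- **That all biologics are pooled, hiding drug-specific signals.** This would be inferred from silence. The article names two ways of describing the biomarkers and excludes no others. The statement that "These algorithms were developed in a population of patients with a previous failure to iTNFs receiving the specific medication the algorithm was designed for" concerns how the prediction algorithms were built, not the M0-to-M6 change in the proteomic profile. The biobank is described as a basis for future studies, not as a search for drug-specific response signals.
- **That an arm difference will reflect the drug menus rather than response.** Nothing in the article reads an arm difference as response, which has its own description by observed response group. The menus overlap. The trial also randomises prescribing strategies, so drug mix is part of the strategy's effect and does not bias the arm contrast. It only limits what that contrast can be taken to mean.

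**Conclusion.** The point holds in a limited form. As worded, the M6 arm contrast leaves out the patient's own M0 level, and this loses precision for any non-zero correlation between the two visits. The unadjusted variance is 10%, 33% or 96% larger than the adjusted variance at ρ = 0.3, 0.5 or 0.7. With the maximum of 90 per arm, the detectable difference would fall from 0.418 SD to 0.398, 0.362 or 0.298 SD. The correlation and full participation are assumptions; the direction of the gain depends on neither.

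The drug-mix point is a caution about interpretation, not a flaw in the randomised comparison, and its size cannot be fixed from the article. Overall this is a minor, free improvement to a secondary substudy outcome, with no consequence for the trial's main conclusions.

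**What to change.** 1. Replace the separate arm comparisons at M0 and M6 with one contrast per biomarker: M6 level on arm, adjusted for M0 level (ANCOVA), on the measurement scale chosen for that biomarker. Keep M0 by arm as description only.
2. Do not add drug received or response group to that model. Both arise after randomisation and depend on arm, so conditioning on them would remove the randomised meaning of the contrast.
3. Separately, and labelled as association, describe M0-to-M6 change by response group within drug class where numbers allow. With at most 90 patients per arm, some cells will be too small for more than a listing.
4. Add a sentence that an arm difference in a biomarker is an effect of the prescribing strategy, including its drug mix, and is not evidence of a response signal.

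The cost is a change of wording in the analysis section. M0 and M6 samples are already scheduled in both arms for consenting patients, and the prescribed drug is known. No new data, visits or patients are needed.

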### Participant timeline {13}

This study will be conducted by rheumatologists who have the opportunity to follow patients with RA and to conduct this study in good conditions and in accordance with regulatory and legal recommendations. The only difference in follow-up between the 2 groups is the addition of the “SinnoTest® Protein Biomarker” assay and the use of the results of this assay for therapeutic management.

Patients will be seen as part of their follow-up consultation in the Rheumatology department:
-Screening: verification of the eligibility criteria.-Inclusion or M0 visit: after information and signature of informed consent. All patients will have a SinnoTest® blood sample. At the end of this visit, the patient is randomized to the SinnoTest® group or the control group. In the control group, the SinnoTest® sample is kept but not analyzed.-6–10 days after the consultation, the prescription of the biotherapy recommended by the rheumatologist is sent by post. This prescription uses SinnoTest® results in the SinnoTest® arm.-Followed quarterly: M3 and M6.

As part of the proteomics substudy, for those patients who agree to participate, blood samples will be collected from the 2 groups in the M0 and in the M6 to study the variations in the proteomic profile of the patients. In addition, the remaining samples will be deposited in a biobank (in the recruitment center and in the Biobank of the Center Hospitalier Universitaire Grenoble Alpes, France). The participant timeline is presented in Table 1.

**Table 1 Tab1:** Schedule of enrollment, interventions, and assessments

Visits	Selection	Inclusion^a^ M0	M3 ± 2 weeks	M6 ± 2 weeks	M12 ± 2 weeks
Information^a^	✓				
Information and consent^b^		✓			
Confirmation of eligibility		✓			
Clinical/physical examination, rheumatoid arthritis		✓	✓	✓	
Routine blood analysis		✓	✓	✓	
Questionnaire EQ5D		✓	✓	✓	
Questionnaire HAQ		✓	✓	✓	
Biomarkers^c^		✓			
Patient booklet^d^		✓	✓	✓	✓
Administration/dispensation of biotherapy^e^		✓			
Biobank^f^		✓		✓	
Concomitant treatments		Collection throughout the study			
Adverse effects collection		Collection throughout the study			

^a^ Inclusion: The inclusion visit should be done in 2–3 weeks

^b^ Information and informed consent: The patient will sign informed consent for the main study and additional consent (optional) if they accept 6-month and 1-year inclusion samples, which will be retained for the creation of biobank

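### The shotgun proteomic comparisons are run biomarker by biomarker at 5% with no multiplicity control, and the arms are also compared at M0, where only chance differences can appear.

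*Protocol article*

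**What the plan says.** The Outcomes section defines the proteomic outcome and the assay: "Based on shotgun and semi-quantitative proteomics, the differences between the proteomic profile at baseline and at M6 will be analyzed". The number of proteins is not given there or elsewhere.

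The proteomic part of the Statistical methods section (its heading is spelled Protomic in the article) sets out three contrasts. The first is within patient: "The biomarkers of the proteomic profile will be compared between the inclusion visit (M0) and the 6-month visit". The other two are between arms: "as well as the differences in both the M0 and M6 visits between the two treatment arms". It then gives the unit of analysis, "The comparison will be done by biomarker", and the error rate, which "is fixed, by convention, at 5% for the different comparative analyses". It names no test or model and no adjustment for the number of biomarkers.

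Participant timeline {13} gives the timing and the population. Of the inclusion visit it says: "At the end of this visit, the patient is randomized to the SinnoTest® group or the control group". The prescription follows 6–10 days later. Participation in the substudy is optional: "for those patients who agree to participate, blood samples will be collected from the 2 groups in the M0 and in the M6".

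**The concern.** Shotgun proteomics is an untargeted assay, so the number of proteins tested is not limited to a small panel named in advance. If each protein is tested at 5%, the expected number of false findings grows in proportion to the number tested, and nothing in the stated rule bounds the proportion of the resulting list that is false. Such a list is weak ground for choosing proteins to follow up.

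The comparison of arms at M0 raises a separate problem. The sample is taken at the visit that ends with randomisation, and the biotherapy is prescribed only afterwards. There is no treatment effect for the test to find, so it can only add chance findings.

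This is a rule that the article states, not a gap left open. An analysis plan that followed the text literally would carry the problem forward.

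**Working it through.** **Inputs from the article.** Error rate 5%; unit of analysis the single biomarker; three contrasts (statistical methods for the proteomic outcome). Assay: shotgun, semi-quantitative (Outcomes). Randomisation at the end of M0 (Participant timeline {13}). The only figure for these comparisons is the 5%. There is no protein count, substudy size or power to reproduce.

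**Assumed, because the article does not give them.** Number of proteins *m*; share of proteins that truly differ, *π*; power per protein.

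**Step 1. Expected false positives when nothing differs.** Expected number per contrast = 0.05 × *m*. This holds whether or not the proteins are correlated.

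| *m* (assumed) | Per contrast | Over three contrasts |
|---|---|---|
| 100 | 5 | 15 |
| 200 | 10 | 30 |
| 500 | 25 | 75 |
| 1,000 | 50 | 150 |

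For proteins said to have changed between M0 and M6, only the per-contrast column applies. The three-contrast total includes baseline arm differences, which are not changes.

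**Step 2. Chance of at least one false positive in a contrast.** With independent tests and no true differences this is 1 − 0.95^*m*: 40.1% for *m* = 10, 92.3% for *m* = 50 and 99.4% for *m* = 100. Correlation between proteins would alter these figures but not those in step 1.

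**Step 3. False share among flagged proteins when some truly differ.** Approximately

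0.05(1 − *π*) / [0.05(1 − *π*) + power × *π*].

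Example, *π* = 10% and power 80%: 0.045 / (0.045 + 0.080) = 36%.

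| *π* (assumed) | Power 80% | Power 50% |
|---|---|---|
| 1% | 86% | 91% |
| 5% | 54% | 66% |
| 10% | 36% | 47% |
| 20% | 20% | 29% |

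The false share exceeds one half when 0.05(1 − *π*) > power × *π*, that is, when *π* < 0.05 / (0.05 + power). The limit is 0.05/0.85 = 5.9% at 80% power, 0.05/0.55 = 9.1% at 50% and 0.05/0.35 = 14.3% at 30%.

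**Step 4. The arm contrast at M0.** Here *π* = 0 by design, so the false share is 100% whatever the power, and about 5% of the proteins tested are expected to be flagged. This assumes that substudy consent is given before the allocation is known. Table 1 fits that assumption, since it places consent at the inclusion visit.

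**Step 5. Under the proposed rule.** Benjamini-Hochberg at 5% within a contrast keeps the expected false share at or below 5%, whatever *m* and *π* are. The guarantee is for independent or positively dependent tests.

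**The case against.** The strongest reply is that the wording sets 5% for the comparative analyses and does not literally say per protein. It does not exclude adjusted p-values or a 5% false discovery rate, and a condensed article may leave the procedure to an analysis plan. The outcome is also headed as a description, with summary indicators and boxplots, and it belongs to a separately consented substudy. Part of this stands: the scope is narrow, and the per-test reading is the natural one rather than the only one. It does not remove the point. The article gives both the unit of testing and the error level with no qualification, and a purely descriptive analysis would need no error level.

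A reader might go further in four ways that the article does not support.

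- **Most flagged proteins are false.** This needs a true share below about 6% to 9% at 80% to 50% power, and neither quantity is stated. Patients start a new biotherapy between M0 and M6, so a larger true share is conceivable in that contrast.
- **The M0 arm tests inflate the list of changed proteins.** They can yield baseline differences, not changes.
- **The M6 arm comparison ignores the M0 value.** No model is named for any proteomic contrast, so neither adjustment nor its absence is stated.
- **The protein list feeds the biobank or the algorithm.** Objectives {7} makes the biobank a basis for the substudy and for later work, and leftover samples are deposited without reference to the results. The Discussion links improvement of the algorithm to clinical validation data in general and does not name the proteomic results.

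**Conclusion.** The point holds as a minor one. As written, the rule leaves the false share among flagged proteins uncontrolled in each of the three contrasts. Its size rests on an assumed protein count: 5 to 50 expected false positives per contrast for 100 to 1,000 proteins with no true differences. The proportion of a reported list that would be false cannot be derived from the article. Under the assumptions tabulated above it runs from 20% to 91%.

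The conclusion on the M0 arm comparison depends on neither the protein count nor the power. In a randomised comparison before treatment, a significant result is chance.

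The consequence stays within the optional proteomic substudy. The primary outcome, the sample size, and the clinical and economic analyses do not depend on it.

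**What to change.** Replace the 5% per-biomarker rule with Benjamini-Hochberg control of the false discovery rate at 5%, applied across all quantified proteins within each contrast, and report the number of proteins tested. Describe the M0 profile by arm without significance tests; two contrasts then remain to be tested.

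Optionally, state that the M6 arm comparison adjusts for the same protein's M0 level. The paired samples are already planned, and this would match the baseline adjustment set out for the clinical secondary outcomes in the Statistical methods section. It is a clarification, not the correction of a stated error.

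The cost is a change of wording, with no new patients, visits or samples. The downside is that fewer proteins will be declared significant, and some with real but modest differences will be missed.
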